### Blinding

The participant, as well as the GP, research nurse, HCA, or RA allocating the patient pack will be blinded to which arm they have been randomised. The patient packs containing either SFJD capsules or placebo capsules are provided in identical packaging to ensure blinding.

An emergency unblinding service is not required for this trial due to the low risk of the Investigation Medicinal Product (IMP) treatments. This has been documented in the trial risk assessment. Any emergency clinical decisions required will not be affected or altered by knowledge of the treatment group allocated to the patient. If unblinding is required this can be done by the Trial Statisticians at the SCTU.

### Intervention

In addition to receiving the current best practice usual care as informed by the local guidelines, participants will receive either 4 × 520 mg capsules of SFJD (Z20090047, batch No. 3210501) or 4 × 520 mg capsules of placebo (batch No. 3210601) identical in appearance: hard capsule, dark brown to reddish-brown granules or powder as content; similar in odour: SFJD aromatic, placebo burnt and aromatic; and different in taste: SFJD bitter, placebo sweet. Both SFJD and placebo are to be taken three times a day, preferably after meals, for a period of 14 consecutive days. The SFJD capsules contain eight herbs (Table 1), with 0.52 g extract, 0.05 g corn dextrin, and 0.05 g silicon dioxide per capsule.

The placebo capsule excipients are corn dextrin (79.66%), caramel (4.62%), food additive lemon yellow (0.35%), compound colourant chocolate brown (0.05%), compound colourant gardenia yellow (0.19%), compound colourant Cocoa Brown (0.23%), naringin (9.62%), anhydrous citric acid (0.96%), menthol (0.96%), FA-10101 sauce flavour essence (2.88%), and MCK135C ginger powder base (0.48%).

A delayed antibiotic prescription strategy will be encouraged by the patients’ responsible clinician; they will be able to offer either immediate antibiotics, delayed antibiotics, or no antibiotics. If antibiotics are prescribed, the choice of antibiotic will be a clinical decision made by the responsible clinician with reference to local guidelines. Common first-choice oral antibiotics for AECOPD include amoxicillin, doxycycline, and clarithromycin [31]. The recruiting GPs will make a clinical decision whether to provide additional treatment, e.g. oral corticosteroids, based on their comprehensive assessment of the patient considering risks and benefits, as per local guidelines.

### Manufacturing process and quality control of the investigational medicinal product

Before the herbs enter the factory, professional and technical personnel check the appearance characteristics of the eight medicinal materials and identify them according to the appearance characteristics specified in CP 2015 to ensure that the herbs are correct. In addition, intermediate products have undergone impurities, identification such as HPLC, microbiology, assay, and description control testing at the company’s laboratory. All eight herbs included in SFJD are processed according to the Chinese pharmacopoeia 2015 Volume 1 (P52/P86/P164/P170/P205/P208/P280) or the Hunan Chinese Herbal Medicine Standard 2009 (P17 for Patrinia Scabiosaefolia). Flowcharts of the manufacturing process including cultivation, harvesting, drying, and cleaning the herbs are provided in Appendix 6.

A sample of each herb was retained and stored in the Central Laboratory Sample Retention Room at Anhui Jiren Pharmaceutical Co., Ltd. Samples are kept at a temperature between 10 and 30 °C and below 35–75% relative humidity. They are packed in sealed polyethylene bags. The retained sample volume of each batch of eight pharmaceutical plant materials is greater than 100 g.

Inspection report of finished product SFJD capsule suggested the product contains emodin (C_15_H_10_O_5_) over 3.0 mg, polydatin (C_20_H_22_O_8_) over 3.0mg, and forsythin (C_27_H_34_O_11_) over 2.0mg per capsule. The shape and properties, identification, content uniformity, and microbiology comply with the specifications according to the China National Medical Products Administration Standard YBZ05182019, 2020 version of Chinese Pharmacopoeia (Inspection Report No.: C-4-018, dated Jun 2021).

Quality assurance processes involving the manufacture, supply, and processing of the herbal medicines, certificates of analysis and stability testing of SFJD and placebo, and transmissible spongiform encephalopathy (TSE) testing and bovine spongiform encephalopathy (BSE) monitoring were performed in China. The trial investigational medicinal product (IMP) was then delivered from China to the UK (Fig. 2). Confirmation quality control testings were performed by ConPhyMed GmbH (Germany) and signed off by a qualified person according to the European Manufacturer’s Good Manufacturing Practice (GMP). IMP dossiers containing safety profile of the product were developed for SFJD capsule and its placebo.

**Fig. 2 Fig2:**
[figure not shown]
EXCALIBUR IMP flow chart

### Trial discontinuation

In consenting to the trial, participants have consented to the trial intervention, follow-up, and data collection. Participants may be withdrawn from the trial procedures at any time, in the event of:Clinical decision, as judged by the principal investigatorThe development of toxicity, regardless of causality, which, in the investigator’s opinion, precludes further treatment under this protocolThe patient withdraws consentNon-compliance with protocol

Full details of the reason for trial discontinuation will be recorded in the eCRF and medical record.

### Outcome measurements and data collection

As this is a feasibility study, only feasibility endpoints will be assessed:

1). Recruitment process and retentionEligibility: Proportion of patients on the COPD register who present with AECOPDEligibility: Proportion of AECOPD-presenting patients eligible and ineligible (plus reasons) for the trialRecruitment/randomisation: Proportion of eligible patients recruited/randomisedRecruitment: Rate of recruitment per month open in the UK primary care settingRetention: Across the duration of the trial

2). Intervention management and proceduresIntervention compliance according to diary data and returned medicationAverage no. of capsules taken per day per patientDuration of treatment per patientDetermine issues around safety and ADR reportingEffectiveness of blinding: Proportion of patients correctly guessing treatment/placebo allocation and reasons why

3). Completion of outcome measuresProportion of diary completionProportion of patients returning trial diariesProportion of patients who took antibiotics in each groupProportion of patients given immediate and delayed antibiotic prescriptions

Participants’ demographic data, their medical history, AECOPD symptoms, COPD Assessment Test (CAT)^TM^ symptom questionnaire, the EXAcerbations of Chronic Pulmonary Disease Tool - Patient-Reported Outcome (EXACT-PRO®) symptom questionnaire, and any adverse events during the trial process will be collected alongside a treatment diary, at various time points (Table 2).

**Table 2 Tab2:** Schedule of observations and procedures

Observation/procedure		Timings of visit/contact						
	Person undertaking the specified event	Screening/registration Days 0–1	Treatment Week 1 Days 1–7	Treatment Week 2 Days 8–14	Follow-up Week 3 Days 15–21	Follow-up Week 4 Days 22–28	Follow-up Week 5 Day 35	End of study Week 12 Day 84
Informed consent	GP/nurse^1^/HCA^1^/RA^1^	**X**						
Eligibility evaluation	GP/nurse prescriber^1^	**X**						
Relevant medical history	GP/nurse/HCA	**X**						
Assess AECOPD symptoms	GP/nurse/HCA	**X**						
Prescribe antibiotics (as appropriate)	GP/nurse prescriber	**X**						
Issue trial medication/randomisation	GP/nurse/HCA/RA	**X**						
Issue treatment/symptom questionnaire diary	GP/nurse/HCA/RA	**X**						
Vital Signs	GP/nurse/HCA	**X**^**9**^						
Completion of CAT^TM^ symptom questionnaire^3^	GP/nurse/HCA/RA/patient^3^	**X**^**3,9**^		**X**^**3**^		**X**^**3**^		**X**^**3**^
Demographic data*	Patient		**X**					
Completion of EXACT-PRO® symptom questionnaire^2^	Patient		**X**	**X**	(**X**)^2^	(**X**)^2^		
Completion of treatment diary	Patient		**X**	**X**	**X**	**X**		
Phone call to patient (questionnaire assessment)^4^	SCTU		**X**^**4**^	**X**^**4**^		**X**^**4**^		**X**
Completion of diary/questionnaire by recall^5^	SCTU and patient						**X**	**X**
Adverse event (AE) notification^6^	SCTU and patient		**X**	**X**	**X**			
AE assessing^6^	GP		**X**	**X**	**X**			
AE recording/reporting^6^	GP/nurse/HCA		**X**	**X**	**X**			
Concomitant medication (only to be recorded in the event of an SAE and specified AEs)^7^	GP/nurse/HCA		**X**	**X**	**X**			
Serious adverse event (SAE) assessing	GP		**X**	**X**	**X**			
SAE reporting	GP/nurse/HCA		**X**	**X**	**X**			
Medical notes review	GP/nurse/HCA							**X**
Qualitative interview (refuse to participate in the trial)^8^	Qualitative researcher	(**X**)^8^						
Qualitative interview (participated in the trial)	Qualitative researcher						**X**^**10**^	

*NR* nurse researcher, *HCA* healthcare assistant, *RA* research assistant

*The relevant demographic and other data to be recorded by the patient on the first day of treatment are as follows: gender, employment, ethnicity, and smoking history

^1^In line with local GP surgery procedures with demonstrable and appropriate level of training. Specific duties delegated by the PI

^2^The EXACT-PRO® symptom questionnaire should be completed daily from day 1 of treatment until either the 14 day treatment is complete and resolution of their AECOPD symptoms have been maintained for 7 days or 28 days post-randomisation

^3^The CAT^TM^ symptom questionnaire should be completed by the patient with the site team staff on day 1 and by the patient in the patient diary on days 14, 28, and 84

^4^Patient phone calls to be completed on days 3, 14, and 28 to ensure the diary instructions provided by the research team at baseline are being followed and to answer any questions the patient has regarding diary completion. The SCTU team follow a trial script to ensure the requirements for collecting data for each endpoint are understood by the patient

^5^Only to be completed if the participant has not returned their participant diary

^6^Only AEs believed related to the trial medication will be recorded on the trial. Reporting and recording of all AEs related to the trial medication is carried out by GP/nurse

^7^Concomitant medication should only be recorded in the event of a serious adverse event or an adverse event related to the trial medication. When an SAE or trial medication-related AE occurs, all concomitant medication that the patient was taking at onset of the event should be recorded in the eCRF

^8^This interview may take place at any time between confirmation of a patient’s refusal to enter the trial and the end of the trial

^9^Vital signs and baseline CAT questionnaire may be completed on day 0 or 1, depending day of provision of patient pack to patient

^10^Qualitative interviews will take place at any time from day 35 onwards

NB: The participant is free to withdraw consent at any time without providing a reason. When withdrawn, the participant will continue to receive standard clinical care. Follow-up data will continue to be collected (unless the participant has specifically stated that they do not want this to happen).

All participant data for the main feasibility trial will be collected and uploaded to the Medidata RAVE® Electronic Data Capture database, which is hosted on servers based in the USA. However, the Medidata team will not have access to the trial data, and no data will be sent outside the UK. Baseline and medical notes review data will be collected and entered onto the database by research site staff, whilst information from the participants’ diaries and questionnaires will be transcribed and entered by the SCTU.

The expectation is for trial participants to complete the 28-day Trial Medication and Symptom diary and then for completion of the final CAT questionnaire and Notes Review to take place on day 84 post-randomisation. As the data collected from participants in the first 28 days are the most critical to the trial, and to maximise overall recruitment, patients will continue to be recruited until 28 days prior to the planned last patient last visit (LPLV) date. These participants will therefore have a truncated follow-up period: participants recruited between 84 and 56 days prior to LPLV will continue to receive their final CAT questionnaires, for completion on the LPLV date; and Notes Reviews will be performed on all participants, but with the period of review shortened to match the LPLV date. All necessary considerations will be made when including these patients in the trial analyses.

At the end of the trial after all queries have been resolved and the database frozen, the PI will confirm the data integrity by electronically signing all the eCRFs. Each PI will receive a copy of the original participant diaries for their site, as these are considered source documents, to allow the full PI oversight of the data. The eCRFs will be archived according to SCTU policy and a PDF copy including all clinical and Meta data returned to the PI for each participant. Data from the qualitative substudy will be transcribed and analysed separately.

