**Methods:**

This study is a phase III, two-arm individually double blind, randomised, placebo-controlled feasibility trial with nested qualitative study, coordinated by the Southampton Clinical Trial Unit (SCTU). Patients aged ≥ 40 years, with a current AECOPD, presenting with increased sputum purulence/volume, or breathlessness, and for whom the GP is considering use of antibiotics, will be eligible to participate. We aim to recruit seven eligible participants per month and randomise them to receive either the patent Chinese herbal medicine SFJD capsules or placebo for 14 consecutive days and to follow-up for 12 weeks. The primary outcomes include the feasibility of recruitment, study retention, and the percentage of diary completion.

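### The text says any adverse event is collected, but Table 2 footnote 6 keeps only those judged related, and AE and SAE capture is scheduled to day 21 of 84

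*Protocol article*

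**What the plan says.** In the protocol article, the section on outcome measurements and data collection states that "any adverse events during the trial process will be collected alongside a treatment diary". The same sentence refers to Table 2 for timing. Footnote 6 of that table sets a narrower rule: "Only AEs believed related to the trial medication will be recorded on the trial".

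The footnote mark sits on the three AE rows (notification, assessing, and "AE recording/reporting^6"). It is absent from the two SAE rows, "Serious adverse event (SAE) assessing" and SAE reporting. Footnote 7, on concomitant medication, names an SAE and a medication-related AE as two separate triggers.

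All five rows are marked in weeks 1, 2 and 3 only, so the last marked column is "Follow-up Week 3 Days 15–21". The table's last column is "End of study Week 12 Day 84", and the abstract describes SFJD or "placebo for 14 consecutive days and to follow-up for 12 weeks". The treatment diary is marked through week 4. Calls fall on days 3, 14 and 28 (footnote 4), with a further call and a medical notes review at day 84. Late recruits have shortened follow-up, but every participant has a notes review.

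Safety enters the endpoint list as a feasibility item on safety issues and the reporting of adverse drug reactions. The Statistical analysis section plans descriptive summaries by allocated group, without formal comparison.

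**The concern.** If an AE is entered only when someone believes the trial medication caused it, attribution stops being a recorded variable and becomes the condition for having a record at all. The AE assessor is the GP, who is blinded and sees one patient at a time. An excess of events on one treatment shows up when all-cause frequencies are set side by side, not in single judgements.

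Attribution is plausibly confounded here. The Background lists gastrointestinal events, dizziness and rash as the minor events reported with SFJD. Entry requires that the clinician is considering antibiotics, and the Intervention section allows them to be prescribed immediately or on a delayed basis. A participant on both could have such an event put down to the antibiotic and left out.

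The time window adds a second limit. An admission or death after day 21 has no scheduled SAE row, although the trial's hypothesis includes admission and relapse. What is at stake is how far the feasibility endpoint on safety can be answered, and what the AE summaries by arm can tell the planners of the full trial.

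**Working it through.** The plan gives no AE rate and no precision figure for safety, so there is no stated number to reproduce. The check sets the rules side by side and counts days.

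**1. Which events are recorded**

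| Source | Non-serious AEs | SAEs |
|---|---|---|
| Outcomes text | any | any |
| Table 2, footnote 6 | only those believed related | footnote not attached |
| Table 2, footnote 7 | related AEs named as one trigger | SAEs named as a separate trigger |

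For non-serious events the text and footnote 6 define different data sets. The text's reference to Table 2 concerns time points and does not turn *any* into *only related*. For SAEs no causality filter is stated.

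**2. When events are recorded**

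Inputs: treatment 14 days (Intervention); last AE/SAE column ends on day 21 and end of study is day 84 (Table 2); shortest planned follow-up 28 days (recruitment continues until 28 days before the planned last visit).

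- Window beyond treatment: 21 − 14 = 7 days.
- Share of full follow-up covered: 21/84 = 25%.
- Uncovered: 84 − 21 = 63 days, and 63/84 = 75%.
- Latest recruits: 21/28 = 75% covered, and 28 − 21 = 7 days (25%) uncovered.

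**3. Match with scheduled contacts**

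No call falls in days 15 to 21. The first call after day 14 is on day 28, outside the AE window. The last week of the window therefore has no scheduled call, and the next call comes when AE capture has closed.

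**4. Size of the causality filter**

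This cannot be computed, because the article gives neither an AE risk nor the share judged related. For illustration only, assume an all-cause AE risk of 10% to 30% and a share judged related of 10% to 50%. With 40 participants per arm:

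- Participants with an AE: 40 × 0.10 = 4 to 40 × 0.30 = 12.
- Participants recorded: 4 × 0.10 = 0.4 to 12 × 0.50 = 6.

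The range shows only that recorded counts could lie well below actual counts. It estimates nothing about this trial.

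**The case against.** Much can be said for the plan. The text refers to the table, so footnote 6 may be the working rule and *any* a loose summary word. The endpoint concerns reporting of adverse drug reactions, which are suspected related events, so recording those suits that part of it. Only feasibility endpoints are assessed, and no all-cause AE rate is specified. A window of treatment plus 7 days is a legitimate choice. Other routes exist: withdrawals for toxicity are recorded whatever the cause, duties for managing serious events are delegated, and every participant has a notes review. These points stand, and they reduce the weight of the concern. They do not settle which AEs sites were meant to record. Nor does the article say that the notes review extracts SAEs, so capture there is neither shown nor excluded.

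Three stronger readings are tempting and not supported:

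- **All safety counts, SAEs included, are causality-filtered.** Footnote 6 is not on the SAE rows, and footnote 7 treats SAEs separately.
- **The filter favours one arm.** The assessing clinician is blinded. The capsules are said to differ in taste, but nothing shows that attribution differed by arm. Undercounting is the supported conclusion.
- **The safety endpoint cannot be met, or a bound on the true AE rate can be obtained by scaling up the recorded one.** Reporting of suspected reactions can still be examined, and the documents give no recording fraction to scale by.

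**Conclusion.** The concern holds in a limited form. The text and footnote 6 contradict each other on which non-serious AEs are recorded. Under footnote 6, non-serious AE counts cover only events a blinded clinician attributes to trial medication, and both AE and SAE data end at day 21. Scheduled capture then misses 63 of 84 days (75%) for participants with full follow-up, and 7 of 28 (25%) for the latest recruits. The 63-day figure matters mainly for SAEs; for non-serious AEs the practical gap is days 22 to 28, while diary and calls are still running.

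This restricts the feasibility endpoint on safety and reaction reporting but does not defeat it: events not attributed to the medication, and later ones, are out of view. The conclusion assumes that Table 2 is the operative schedule and that the notes review does not already extract SAEs. If it does, the SAE part falls away once that is stated. The loss due to the causality filter cannot be quantified from the document.

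**What to change.** 1. Reconcile the outcomes text with footnote 6. Record every patient-reported AE to day 28 through the existing diary and the day 3, 14 and 28 calls, with relatedness as a separate field completed blind. The calls are now described as diary support, so their script would need an AE question.
2. Extend SAE capture by extracting admissions and deaths from the planned notes review, to day 84 or the shortened last-visit date, and say so in Table 2.
3. Summarise all-cause and related events by arm, descriptively, in line with the plan's decision to make no formal comparison.
4. The article reports that data collection finished in September 2022, so prospective AE capture can no longer be added. If footnote 6 was applied, state this, label the AE results *judged related only, to day 21*, draw no conclusion on overall AE rates, and carry all-cause capture into the full trial.

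The cost of items 1 to 3 is modest extra data entry for 80 patients at contacts and a review already scheduled. Item 4 costs only wording in the report.

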### Statistical analysis

Study data will be entered onto SPSS (v.25) for data cleaning, coding, and analysis. The analysis of this feasibility trial will be mainly descriptive focusing on estimation rather than hypothesis testing. All baseline measures and outcomes will be summarised for each allocated group using the appropriate descriptive statistics. No formal comparison of groups will take place. A full statistical analysis plan will be developed prior to the final analysis of the trial.

### Trial oversight groups

The day-to-day management of the trial will be co-ordinated through the SCTU and oversight will be maintained by the trial management group and the trial steering committee. No independent data monitoring or data monitoring and ethics committees will be convened for this trial. These roles will be assumed by the trial steering committee.

### Patient and public involvement

The EXCALIBUR trial has benefitted from patient and public involvement (PPI). The trial management group (TMG) has two PPI members [JH, NG]; the trial steering committee has one PPI member [EC]; and a further two PPI members [DS, PH] were consulted alongside the TMG members when developing the protocol and trial materials, such as the participant diary. They have provided additional advice on the trial design, the protocol, and patient-facing study documentation. Potential barriers to participation and the outcome relevant to patients were discussed with them thoroughly, in consideration of the COVID pandemic situation. PPI will continue throughout the conduct of the trial.

We plan to utilise the skills of our PPI representatives to help interpret the qualitative data and to reflect on changes which may enhance recruitment and retention to the full trial if necessary. At the end of the study, it is important that the findings reach patient/public audiences and that the clinical audiences hear from the public voice; hence, we will include our PPI representatives in relevant presentations and/or articles to ensure maximum impact.

